### Study outcomes

#### Primary outcome

The primary outcome in this study is a summary composite metric of poor childbirth outcomes. The component outcomes of the summary outcome are those anticipated to be preventable by the correct utilization of the modified WHO-SCC. They will encompass in this study: stillbirths, maternal deaths, early neonatal deaths, severe postpartum hemorrhage, maternal infections, early neonatal infections, prolonged obstructed labor, severe pre-eclampsia, uterine rupture in the health facility, eclampsia and maternal near miss. The definitions for the above severe complications are based on WHO clinical and laboratory-based criteria [22].

The presence/absence of each of the above poor childbirth outcomes will be ascertained in each birth event using data extraction from registries and patients’ charts. Different data sources will be used to cross-validate the information. These include birth registries, partograph, temperature sheet and mothers’ health books.

Regarding all these items the standards in all countries are anticipated to be similar. Other secondary outcomes that will be analyzed separately include the use of transfusion services and the return within 7 days to the health facility after discharge for complications related to the mother or the new-born. Two waves of supplies ‘availability assessments (initial assessment prior to the launch of the intervention and final assessment at the end of the study) will be conducted in both intervention and control health facilities.

#### Secondary outcomes

The first secondary outcome is the level of adherence to EBPs by healthcare providers during childbirth and early postpartum. This will be measured as a rate of successful delivery of key EBPs included in the modified WHO-SCC at each birth event. The provision of key EBPs will be ascertained in a sample of birth events using direct observation with possible cross-validations with data from birth registries and mothers’ health books when necessary. The anticipated best practices to be assessed in this study include: the assessment for need of reference, the use of a partograph, assessment for history and actual bleeding, vision blurred, HIV status, correct use of magnesium sulfate, uterotonics and antibiotics, early initiation of breastfeeding and skin-to-skin contact, and discussions around family planning services.

The second secondary outcome is the rate of availability of essential safe childbirth supplies measured at health facility level. A facility assessment questionnaire will be used to collect data on the availability of essential safe childbirth supplies as baseline assessment prior to the onset of the study. Six months after the launch of the study an end line survey will be conducted using the same questionnaire.

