## Methods

### Trial design

The intervention will be delivered at health facility (cluster) level and outcomes measurements will be carried out at individual participant level. We will use a matched paired cluster randomized controlled trial design, where a pair of health facilities (one intervention and one control) are enrolled in the study at the same time. The study will be conducted in referral hospitals with gynaecologists and where surgical facilities for c-section and blood transfusion services are readily available. Eight (8) regional hospitals (4 intervention and 4 control sites) will be included in the study in each country, giving a total of 24 health facilities (12 in intervention and 12 in control arms) in the three countries. Within each matched pair of health facilities, one will be randomized to receive the intervention and one will receive the standard of care. Facilities will be matched using geographic location within the country, the size of the population covered by the health facility and the annual births volume of the facility. The study will combine two main components: a data extraction component (used to measure the incidence of poor childbirth outcomes) and a direct observation of childbirth practices (to assess the availability of safe childbirth supplies and the adherence of care providers to EBPs).

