### Statistical methods

The analysis will be per intention to treat. Descriptive statistics for the study sample will be computed using means and standard deviations or medians and interquartile ranges (IQR) for continuous covariates, and proportions will be used to describe categorical variables. We will make use of the Rao-Scott chi-square test statistic, which adjusts for the matched-pair, cluster randomization scheme [24], to compare the rates of the primary and secondary outcomes in the comparison and intervention groups if the randomization scheme was found effective. Possible multivariable modeling techniques to correct for potential imbalances between study groups include Generalized estimating equations, multilevel Poisson modeling and multilevel cox models. The data analysis will be carried out using Stata 15.1 software. A *p*-value< 0.05 will be necessary to consider intervention and comparison groups significantly different.

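### Supply availability is measured before launch and at end line in all hospitals, but the one test stated for it has no baseline term, leaving the comparison avoidably imprecise

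*Protocol article*

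**What the plan says.** The protocol article, under Secondary outcomes, defines the outcome: "The second secondary outcome is the rate of availability of essential safe childbirth supplies measured at health facility level". The first wave is described there as "A facility assessment questionnaire will be used to collect data on the availability of essential safe childbirth supplies as baseline assessment", and the second as "Six months after the launch of the study an end line survey will be conducted using the same questionnaire". The text under Primary outcome gives the same two waves ("initial assessment prior to the launch of the intervention and final assessment at the end of the study") and states that they "will be conducted in both intervention and control health facilities".

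On numbers, Trial design says: "Eight (8) regional hospitals (4 intervention and 4 control sites) will be included in the study in each country". That is 24 hospitals over three countries. On allocation it says: "Within each matched pair of health facilities, one will be randomized to receive the intervention and one will receive the standard of care". The matching factors listed there are location, population covered and birth volume; supplies are not among them.

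Statistical methods names a Rao-Scott chi-square test, adjusted for the matched-pair cluster scheme, "to compare the rates of the primary and secondary outcomes in the comparison and intervention groups", provided that randomisation is judged to have worked. Multivariable models (generalized estimating equations, multilevel Poisson, multilevel Cox) are listed as possibilities for correcting imbalance between groups. The baseline supply value is not mentioned in that section.

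**The concern.** Improving supply availability is one of the three stated objectives. Each hospital supplies one availability rate per wave, so there are 8 end-line values per country and 24 overall. With so few units, a baseline measure of the same quantity is usually the most useful covariate available, and here it is collected in every hospital. The stated default test gives it no role. The fallback models come into play only after a judgement about imbalance, whereas adjustment for a baseline value of the outcome is best fixed in advance, whether or not imbalance is seen.

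What is at stake is precision. Part of the spread in end-line availability will reflect each hospital's starting stock, and the stated comparison leaves that part in the error term.

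**Working it through.** **The plan's own figures.** The article gives no power or sample size for the supply outcome; Sample size covers only poor childbirth outcomes and adherence. The primary figure is not in dispute. For 15% against 7.5% with continuity correction, 304 per arm × design effect 1 + 299 × 0.01 = 3.99 gives 1,213, against the stated 1,200. Then 1,200 / 0.95 = 1,264 per arm, or 2,528 per country, against 2,530.

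**Inputs.** Number of pairs k: 4 per country, 12 overall (Trial design). Two-sided 5% level and 80% power, borrowed from Sample size. Correlation r between a hospital's baseline and end-line values: not given, assumed 0.3 to 0.9. Matching is assumed to bring no gain, so the end-line difference within a pair has variance 2 in units of the squared between-hospital SD.

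**Formulas.** The detectable difference solves power = 0.80 under a noncentral t with standard error √(V/k):

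- End line only: V = 2, df = k − 1.
- Change score: V = 4(1 − r), df = k − 1.
- Baseline-adjusted: V = 2(1 − r²), df = k − 2.

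Adjustment therefore multiplies the residual variance by 1 − r², which is 0.91, 0.75, 0.51 and 0.19 at r = 0.3, 0.5, 0.7 and 0.9.

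**Detectable difference in SD units**

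| Analysis | r = 0.3 | r = 0.5 | r = 0.7 | r = 0.9 |
|---|---|---|---|---|
| 12 pairs, end line only | 1.26 | 1.26 | 1.26 | 1.26 |
| 12 pairs, change score | 1.49 | 1.26 | 0.97 | 0.56 |
| 12 pairs, baseline-adjusted | 1.21 | 1.10 | 0.91 | 0.55 |
| 4 pairs, end line only | 3.01 | 3.01 | 3.01 | 3.01 |
| 4 pairs, change score | 3.56 | 3.01 | 2.33 | 1.35 |
| 4 pairs, baseline-adjusted | 3.81 | 3.46 | 2.85 | 1.74 |

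**Degrees of freedom.** Pooled with country terms: 24 − 1 (intercept) − 1 (arm) − 2 (countries) = 20, and 19 with the baseline. Pooled with pair terms: 24 − 12 − 1 = 11, and 10 with the baseline. One country with pairs: 3, and 2 with the baseline.

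**Break-even on interval width.** With 4 pairs the t multiplier rises from 3.18 to 4.30, so adjustment gains only if r > √(1 − (3.182/4.303)²) = 0.67. With 12 pairs it rises from 2.201 to 2.228, and the break-even is about 0.16.

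**A limit of these figures.** They take the baseline slope as known apart from the lost degree of freedom. Estimating it inflates the variance on average by 1 + 1/(k − 3) when pairs are kept. For 12 pairs that is 1 + 1/9 = 1.11, or a factor of √1.11 = 1.05 on the detectable difference: about 1.28, 1.16 and 0.96 SD at r = 0.3, 0.5 and 0.7. So with pair terms the gain at r = 0.3 disappears, while the gains at 0.5 and 0.7 remain. For 4 pairs the inflation is 1 + 1/1 = 2, which strengthens the case against a paired regression in one country.

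**The case against.** Much of the case on the other side is fair.

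- A reader might infer that the baseline is to be discarded. The article never says so. Two waves with one questionnaire and an objective framed as improvement suggest that the authors mean to use it, and the optional models leave room for it. What stands is narrower: the stated default test has no baseline term, and no passage gives the baseline supply value a role in the analysis.
- A reader might infer that a baseline difference between arms would be taken for an effect. Allocation is random within pairs, so a chance difference adds variance, not bias, and a valid test allows for it. That supplies are not a matching factor makes such a difference possible; it does not show it to be likely.
- A reader might infer that the end-line comparison has the worst precision available. The table contradicts this: with 4 pairs it beats paired regression at r = 0.3 and 0.5, and the change score at r = 0.3.
- The pooled gain presupposes a 24-hospital analysis, which the article does not state. It describes and sizes the trial by country.
- The article is condensed, and covariates are commonly left to an analysis plan. That would dispose of the point if the article were silent, but it fixes a test for the secondary outcomes.
- Trial design places supply assessment within the direct-observation component, and a rate over listed items could be analysed as items clustered within hospitals, which a Rao-Scott test can handle. The randomised units would still be the 24 hospitals, and the baseline would still have no place in the test.

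**Conclusion.** The point holds as an available improvement to a secondary analysis. The stated end-line comparison is valid on average but avoidably imprecise, because a baseline value of the same outcome is collected in all 24 hospitals and the stated test does not use it. With 12 pairs, the detectable difference falls from about 1.26 SD to 1.21, 1.10 or 0.91 SD at r of 0.3, 0.5 or 0.7. This rests on an assumed r (once country or pair is in the model, the correlation given those terms), on no gain from matching, and on pooling the three countries. At low r the gain is slight or nil. The weight is modest: this is the second secondary outcome, no figure in the article is wrong on this account, and the primary analysis is untouched.

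**What to change.** In Statistical methods, replace the Rao-Scott test for this outcome with a prespecified model. For each hospital, compute the percentage of listed supplies available at each wave. Fit a linear model of the end-line percentage on arm, baseline percentage and country (or matched pair), pooled across all 24 hospitals, with t-based inference. Apply the adjustment whether or not imbalance is seen.

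Do not fit the paired regression separately within a country of 4 pairs, where it loses precision unless r exceeds about 0.67. A change score there gains only above r = 0.5. Per-country results are better given descriptively: an exact paired sign-flip test on 4 pairs cannot go below a two-sided p of 2/2⁴ = 0.125.

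The cost is a sentence or two of text, one degree of freedom (of 20 with country terms, of 11 with pair terms) and a stated decision to pool for this outcome. No new data are needed.

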### Sample size

Different sample size calculation will be carried out for different study outcomes.

#### The incidence of poor childbirth outcomes

The component outcomes of the summary primary outcome are relatively infrequent events. Looking at recent health system information data from the three countries, we estimated that at least one of the component outcomes would be observed in an average 15% of vaginal deliveries in the study settings. With a bilateral type I error set at 5%, and a half reduction in the incidence of the primary outcome for the intervention group considered sufficient to prove the effectiveness of the intervention, we would need to observe a minimum of 1200 childbirths in each group (4 clusters per group) for a statistical power of 80%, assuming an intra-class correlation coefficient of 0.01 [23] and an average cluster size of 300. The calculated sample size was adjusted for a non-response rate of 5%. The final required sample size per country is therefore of 2530 childbirth events, half in each trial arm.

#### The adherence to EBPs

Based on the results of a formative research that showed important variations (ranging from very low to very high) in the adherence to EBPs in Burkina Faso and Côte d’Ivoire (unpublished data), we assume an average and conservative adherence of 50%. Considering a type I error level of 5% and taking into account the study design, a sample size of 620 childbirth events would be necessary in each country to detect an effect size of 15 percentage point with a statistical power of 80%.

### Data collection and follow up procedures

Two data collection techniques will be used: a direct observation of healthcare providers’ performance of best practices and data extraction from various source documents to assess childbirth outcomes.

#### Direct observations

Data collectors with a medical background (nurses, midwives or medical students) will be recruited and trained by the research team in each country. The data collectors will not be staff members of the participating health facilities and will be solely appointed in the health facility for the purpose of the study. Medical students are those in the last year of their medical studies and that are awaiting the defense of their thesis. The trainings will last for 3 days in each country and include orientation to the WHO-SCC, mastering of the questionnaire through in-room role-plays and field testing. The data will be collected using a standardized questionnaire performed into electronic devices (tablets or smartphones). The questionnaire will capture in addition to the information on the items included in the modified WHO-SCC, the socio-demographic characteristics of the mothers and new-born along with that of health care providers. To achieve the calculated sample size, we anticipate the observation of 80 childbirth events in each health facility. Considering a minimum average of 2 eligible childbirth events per health facility and per 24 h, the observation will last for a maximum of 45 days in each health facility.

Two data collectors will be appointed permanently (day and night) in each regional hospital during the period of data collection to directly observe and document the healthcare providers’ practices. The observations for each birth event will take place at four critical junctures from admission to discharge: at the admission, before the woman starts pushing, soon after delivery and just before discharge from the hospital. The observation will be strictly passive with no interaction with the healthcare providers and the patients. However, the data collectors can alert the healthcare providers in the event of occurrence of a life-threatening complication. Furthermore, should healthcare providers not adhere to a standard putting mother-new-born pair at high risk (examples: no administration of ARTs, antibiotics, sulfate of magnesium when needed), the observer will intervene in a kindly manner to suggest that such practice may be worthwhile. The intervention of the observer will follow a suggestive process without any coercion on the healthcare provider being observed. In such a case it will be recommended to probe the healthcare provider questioning the relevance of such a practice. For example, what do you think of the administration of ARTs to this woman? Would that be relevant? The healthcare provider must not be driven to feel guilty or blamed for anything. Any suggestion deemed relevant will be made in an inconspicuous manner, meant to be a private communication between the observer and the relevant healthcare provider. If an EBP was adhered to only after a suggestion was made by the data collector, her/she will still record that particular EBP as not having been adhered to by the healthcare provider.

The observation will be conducted every day of the week and at any time without discontinuation until the target sample size is achieved. A data collector may observe only part of a birth event and the observation will be continued by another data collector. However, data on each critical juncture must be fully collected by the same data collector. Thus, once a data collector has initiated the observation for a given pause points, he/she can get off work only after having filled in all the items pertaining to that pause point.

#### Data extraction

The data extraction will be carried out using a standardized questionnaire performed into electronic devices. Using different sources of information including a modified birth registry, patients charts and maternal health books where available, we will collect socio-demographic and childbirth outcomes data in both control and intervention health facilities on all consecutive eligible women that were admitted for labour and delivery from 2 weeks after the launch of the intervention to 8 months. The data extraction in each health facility will be conducted twice-weekly by facility-based trained coaches. They will review data source documents to collect information on each eligible mother-new-born pair from admission to 7 days after delivery. Based on the calculated sample size, we will need to include and extract data on 320 childbirth events in each health facility. Based on the minimum average of two childbirths events per 24 h, each health facility is expected to have cared for at least 320 pregnant women in 6 months from the launch of the study.

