### Intervention

The intervention will encompass: (i) the introduction of a modified WHO-SCC in health facilities, (ii) trainings of healthcare providers on good childbirth practices, (iii) and ongoing supportive supervisions. The modified WHO-SCC, as a job aid tool that prompts healthcare providers to remember EBPs that a woman and/or her new-born must receive at four critical junctures during intrapartum and immediate postpartum periods, will be adapted from the WHO-SCC to reflect local contexts and align to the national guidelines of each implementing country. Based on the results of the formative research that showed that the implementation of the WHO-SCC would be more effective if healthcare providers are trained on EBPs complemented by supportive supervisions, the modified WHO-SCC will be introduced in intervention health facilities following a coaching-based approach [12–14, 21]. The formative research also suggested that the content and the ordering of the items of the WHO-SCC should be revised to reflect local practice [17]. This adaptation process will be led by a Technical Advisory Group (TAG) that includes the research teams, the ministries of health and the associations of gynaecologists and paediatricians in each country. The content and wording of the items to be included in the WHO-SCC will be first reviewed and validated by the TAG in a one-day meeting. The resulting WHO-SCC will be pilot tested, and the results will be presented to the TAG in another one-day meeting for the finalization of the WHO-SCC to be implemented in each country. For the introduction of the WHO-SCC in health facilities we will use the coaching based approach with the change model that includes Engage, Launch and Support. Prior to the introduction of the checklist in each health facility, we will engage the administrative and medical leaders to discuss the current deficiencies in the delivery of EBPs to women and new-borns in the intrapartum and postpartum periods and the need for a quality improvement intervention. The results of the formative phase showed important quality-gaps in maternity care. The content of the training sessions will be informed by these quality-gaps and we will put more emphasis on areas needing more improvements. The head medical officer of the maternity ward along with the most experimented midwife in each intervention health facility will have a 2-day orientation training to the modified WHO-SCC and EBPs during childbirth. The trained midwife is meant to be the facility-based coach for day-to-day follow up of the utilization of the checklist after the launch. A one-day orientation session to the WHO-SCC will be organized on site for the staff members of each intervention facility and will be run by the head medical officer, the trained midwife with the support from the research team. After the introduction, the support will be assured by the facility-based coach who will identify barriers to the utilization of the checklist including issues with supplies and help overcome them on a day-to-day basis. New staff members appointed in the facility after the launch will automatically benefit from a 1-day orientation session leads by the head medical officer and the trained facility-based coach. The modified WHO-SCC will be introduced in intervention facilities using a combination of two approaches that were identified as the most effective and acceptable ways for its introduction during the formative research. The first way is to reproduce the modified WHO-SCC in a larger format that will be displayed in the delivery room at the bedside of the woman, allowing healthcare providers to have a glance on it at any time while caring for the mother-new-born pair. Similar approaches are used with the guidelines for the management of post-partum hemorrhage and were found effective by most of the healthcare providers during the formative phase. This approach, while effective in prompting on EBPs at any time, does not however, allow the utilization of the modified WHO-SCC as a documentation tool of EBPs in addition. To allow the utilization of the modified WHO-SCC as a documentation tool as well, we will combine the displaying in delivery room with the attachment of a copy to the partograph.

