
### Control group

The standard of care will prevail in the control health facilities. There is no childbirth checklist, or a similar tool being used at the moment in health facilities in all the three countries.

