All the women who were admitted in the child birthing room for elective caesarian section (before the labour has begun);All the women and their newborns that were transferred for additional care after a delivery outside of the participating health facility and those received for any other type of obstetric care not related to childbirth (abortions, miscarriages and antenatal care);Pregnant women referred to higher level of care upon admission without proper administration of care at the level of the participating health facility;Mother-newborn pairs for whom provider was prompted to adhere to best practices in order to prevent a life-threatening situation during the direct observation of childbirth practices.

The recruitment will be done by appointed data collectors in each health facility (direct observation) and the facility-based coaches (data extraction). The enrolment into the study for the direct observation of care practices will take place right at the admission in the health facility, before the initial examination is performed. The process of consenting participant will, however, not be caused to delay the health care and for participants that were not able to provide informed consent before initial examination we will not collect data for this pause-point. Data will be collected for the subsequent pause-points if we get informed consent from the women after initial examination. For the data extraction component of the study, the mother-newborn pairs will be consecutively recruited from 2 weeks after the launch of the intervention to 6 months or until the prespecified sample is reached for each health facility. For the direct observation of childbirth care practices, a sample of mother-new-born pairs will also be consecutively recruited among those admitted for childbirth labour in each health facility. This recruitment will start 2 months after the onset of the intervention in intervention facilities and will continue until the calculated sample size for each health facility is achieved.

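### The primary outcome is recorded by the facility-based coach, who is defined only as part of the intervention; the control-arm extractor is undefined, so outcome recording may differ by arm

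*Protocol article*

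**What the plan says.** The Primary outcome section bases the composite of eleven poor childbirth outcomes on extraction from registries and patient charts. Two places name the person who does this work:

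- Study participants and recruitment: "The recruitment will be done by appointed data collectors in each health facility (direct observation) and the facility-based coaches (data extraction").
- Data extraction: "The data extraction in each health facility will be conducted twice-weekly by facility-based trained coaches". The same section says that data are collected in both arms.

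The coach is defined once, under Intervention. There, "the most experimented midwife in each intervention health facility will have a 2-day orientation training to the modified WHO-SCC and EBPs during childbirth", and "The trained midwife is meant to be the facility-based coach for day-to-day follow up of the utilization of the checklist after the launch". This midwife also helps to run the staff orientation and to remove barriers to checklist use.

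For the other arm, the Control group section says: "The standard of care will prevail in the control health facilities". It mentions no coach.

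The stated safeguards are a standardized questionnaire, consecutive inclusion, WHO-based definitions, cross-validation across sources and, under Quality control, common training, standard case definitions and a weekly double-check of 5% of completed cases.

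**The concern.** In intervention hospitals, the person charged with making the checklist work also applies the exclusions and records whether each woman or newborn had a poor outcome, knowing the allocation. In control hospitals, the text leaves two readings:

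- There is no coach, and somebody of another, unnamed kind extracts the primary outcome.
- There is a coach, and a role that belongs to the intervention has entered an arm meant to receive only standard care.

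Either way, the plan does not secure that the primary outcome is ascertained alike in the two arms. If recording differs, the trial estimates the checklist's effect mixed with the recording difference, and none of the analyses under Statistical methods can separate the two. An implementer's stake could lower the recorded rate. A coach's training could make recording more complete and raise it. The sign is therefore not known in advance.

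**Working it through.** **1. The roles side by side**

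| Question | Intervention hospitals | Control hospitals |
|---|---|---|
| Is a coach defined? | Yes, the trained midwife (Intervention) | No (Control group: standard care only) |
| Who extracts the primary outcome? | The coach | "Coach" by the wording of Data extraction; no such person is defined |
| Is the extractor independent of the intervention? | No | Cannot be told |
| Is the extractor masked? | Not stated; the coach's own duties rule it out | Not stated |

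By contrast, the Direct observations section requires that the observers, who measure adherence (a secondary outcome), are not facility staff. No such rule is given for the primary outcome.

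**2. The plan's own sample size**

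Inputs from the Sample size section: 15% against 7.5%, two-sided 5%, power 80%, intra-class correlation (ICC) 0.01, 300 births per cluster, 4 clusters per group, non-response 5%.

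- Design effect = 1 + (300 − 1) × 0.01 = 3.99.
- Two proportions with continuity correction: 304 per group. 304 × 3.99 = 1213, against 1200 stated. Without the correction: 278 × 3.99 = 1109.
- 1200 / 0.95 = 1264 per group, or 2528 per country, against 2530 stated.

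The figures reproduce closely, so the same inputs can serve for the illustration.

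**3. What a recording difference would do (illustration)**

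Assumptions that are not in the documents: true risk 15% in both arms, complete recording in control hospitals, and a fraction s of events recorded in intervention hospitals. The apparent risk ratio is then s. Any gain in precision from matching is ignored.

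For s = 0.80 the recorded risks are 0.15 and 0.15 × 0.80 = 0.12.

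- Effective size per arm and country = 1200 / 3.99 = 301.
- Standard error = √[(0.15 × 0.85 + 0.12 × 0.88) / 301] = 0.0278.
- Difference / standard error = 0.03 / 0.0278 = 1.08.
- Chance of a significant false benefit, normal approximation: Φ(1.08 − 1.96) ≈ 0.19.
- The same with four pairs and a t-test on 3 degrees of freedom (critical value 3.18, noncentrality 1.08): ≈ 0.12.
- Without bias, the chance in that direction is 0.025.

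| Recorded in intervention arm | Apparent risk ratio | False benefit, one country, normal approximation |
|---|---|---|
| 90% | 0.90 | 8% |
| 80% | 0.80 | 19% |
| 70% | 0.70 | 38% |

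If the three countries were pooled (12 pairs, 9 degrees of freedom), the standard error for s = 0.80 would be 0.0278 / √3 = 0.0161, the noncentrality 1.87 and the chance about 39%. The protocol does not state a pooled analysis.

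**4. The opposite direction (illustration)**

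Suppose the checklist truly halves the risk, recording is complete in intervention hospitals, and control hospitals record 90%, 80% or 70% of events. The apparent risk ratio is 0.075 / 0.135 = 0.56, 0.075 / 0.12 = 0.63 or 0.075 / 0.105 = 0.71. Power per country (normal approximation) falls from 83% to about 67%, 46% or 25%.

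**The case against.** The strongest reply is that the extractor has limited discretion. Inclusion is consecutive, the form is standardized, severe complications follow WHO clinical and laboratory criteria, sources are cross-checked and 5% of cases are re-checked weekly. Deaths, stillbirth, uterine rupture and eclampsia leave little to judgement. Much of this stands, and it limits the likely size of any bias. It does not close the gap. None of these safeguards is said to be masked or carried out by someone other than the coach. The training and re-check under Quality control are written for data collectors, a term that the recruitment text separates from coaches. Five per cent of 320 births is 16 per hospital. Infection, prolonged obstructed labour, severe haemorrhage and near miss rest more on judgement from the chart.

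A reader might infer three stronger things that the documents do not support:

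- That recording does differ by arm, or that control hospitals have no such extractor. No section says either; the Data extraction wording covers every facility.
- That the checklist copy attached to the partograph feeds the outcome. The reason given is "To allow the utilization of the modified WHO-SCC as a documentation tool as well", and what it documents is practices, not outcomes. The list of sources ("These include birth registries, partograph, temperature sheet" and mothers' health books) names the partograph but not the checklist. Fuller charts in one arm are possible but not stated.
- That 39% is the false-positive risk. That figure needs a pooled analysis which the protocol does not state; the design and sample size are set out per country.

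It is also true that source charts are written by unmasked staff whoever extracts them.

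**Conclusion.** The point holds as a conflict of roles and an undefined role. In intervention hospitals the primary outcome is ascertained by an unmasked implementer. In control hospitals the extractor is either undefined or at odds with the Control group section. This is what the article states, not a detail left to a fuller document. That recording may differ by arm is an inference from role and stake, and its size and sign are unknown. Under an assumed 20% under-recording in the intervention arm and no true effect, the apparent risk ratio would be 0.80, with a 12% to 19% chance per country of a false significant benefit (2.5% without bias). At 10% under-recording the normal approximation gives about 8%. These figures show sensitivity; they do not estimate the bias. The passages should be reconciled before recruitment, because extractor bias is hard to repair afterwards.

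**What to change.** 1. In Study participants and recruitment and in Data extraction, replace the coaches with existing facility staff who have no checklist duty, in the same role and with the same training in both arms.
2. Have them enter raw findings (for example vital status, blood loss, temperature, blood pressure, transfusion), and derive the composite by a program that applies the WHO criteria with arm masked.
3. State that the checklist copy attached to the partograph is not an outcome source.
4. Apply the existing weekly 5% double-check to the extracted composite. The research team, not the coach, should do it, masked where feasible, and agreement should be reported by arm.

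The cost is some training, staff time and programming. Using the external observers instead would be dearer: they are planned for at most 45 days per hospital, whereas extraction runs for 6 to 8 months. Masked re-checking may not always be possible where the checklist is attached to the chart. Because unmasked staff still write the source charts, the change reduces the bias and does not remove it.
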